### Intervention

The intervention is described in accordance with the TIDieR (Template for Intervention Description and Replication) checklist and guide [37]. Multimedia Appendix 1 shows the TIDieR checklist. As applicable, this protocol has been developed in accordance with the JMIR CONSORT-EHEALTH (Consolidated Standards of Reporting Trials of Electronic and Mobile Health Applications and Online Telehealth) checklist [38]. Multimedia Appendix 2 shows the JMIR CONSORT-EHEALTH checklist.

### Name and Rationale

The intervention is called YumABLE, and it addresses the effectiveness of using technology to deliver DSME for this target group. The name “YumABLE” reflects the program’s goal of empowering individuals with permanent physical disabilities to be “able” to manage their diabetes effectively, without limitations imposed by their disability. The key components of the intervention include a group class led by a single CDCES, ensuring a personalized experience for participants.

### Materials

Informational materials are distributed during the intervention. Informational materials consist of weekly resources on topics that include nutrition, meal plan methods, shopping tips, and a roadmap to managing diabetes, all provided by the CDCES.

### Procedures

Following randomization, the CDCES conducts a 60-minute one-on-one assessment with each participant via telephone. Subsequently, participants are assigned to a cohort for the 4 weekly 90-minute DSME group classes. Four optional 90-minute make-up classes are available along with a 60-minute follow-up session conducted 3 months after the final DSME coaching session. The intervention arms and treatment are summarized in Table 2.

**Table 2 table2:** Study arms and intervention components.

Participant group or arm	Intervention or treatment
High-technology intervention group	Receive an initial 60-minute 1:1 call with the CDCES^a^. Receive 4 weekly 90-minute remote DSME^b^ classes with the option to make up any missed class. Receive one 60-minute follow-up class 3 months after their last DSME class. Weekly diabetes-related materials delivered through multiple modalities (email, text, and telehealth platform), regular text reminders (to read material, track health data, motivation, etc), bidirectional text messaging to enable timely communications with the health coach. Have access to the telehealth platform.
Low-technology intervention group	Receive an initial 60-minute 1:1 call with the CDCES. Receive 4 weekly 90-minute remote DSME classes with the option to make up any missed class. Receive one 60-minute follow-up class 3 months after their last DSME class. Receive 1 weekly email containing diabetes-related materials, bidirectional email communication with the CDCES. Have no access to the telehealth platform.
Attention control group	Receive an initial 60-minute 1:1 call with the CDCES. Receive 4 weekly 90-minute remote DSME classes and with the option to make up any missed class. Receive one 60-minute follow-up class 3 months after their last DSME class. Not be provided with any additional related content or access to technology-based support resources. Have no access to the telehealth platform.

^a^CDCES: certified diabetes care and education specialist.

^b^DSME: diabetes self-management education.

### Intervention Provider

A single CDCES, a board-certified registered nurse with over 15 years of clinical care, education, and health promotion experience, delivers all 4 remote DSME classes, encouraging active participation and reflection. Weekly goals are established and discussed, and troubleshooting is reviewed. Motivational interviewing promotes behavior change and sets personal health goals related to diabetes. The 4 DSME classes included nutritional management and diet, physical activity, medication adherence, and stress management components.

### Modes of Delivery

The classes are conducted remotely. The intervention consists of using pop-up quizzes or polls within each class session, having open discussions, and following up with participants, with communication based on their randomization group.

### Location

The intervention is conducted via video teleconferencing, providing an easily accessible platform for participants. This approach was particularly beneficial for individuals with physical disabilities, as it eliminated the need for travel to a physical location.

### Frequency and Duration

The intervention is for 6 months and includes 4 scheduled classes held consecutively over 4 weeks via video teleconferencing, 4 make-up classes for participants unable to attend an earlier class, and 1 follow-up class. Ideally, each participant would attend 5 sessions during this 6-month period.

### Tailoring and Modification

The intervention includes 3 participants with visual impairments; however, no changes are made to the intervention itself. Instead, materials are adapted to meet participants’ needs. Adaptations include providing the recorded class presentations with audio to participants who request it, weekly resources provided in larger text, and CDCES providing visual cues of the slides during the class to ensure that all participants understand what is being presented. Additionally, the video teleconferencing platform included accessibility features, such as captions for participants with impaired hearing, to ensure that they could fully participate.

### Ethical Considerations

The study was approved by the institutional review board (IRB) of the University of Alabama at Birmingham and is registered on ClinicalTrials.gov (NCT06049225). Informed consent from participants is required for participation in this study. Any modifications to the protocol will be communicated to all relevant stakeholders. The full trial protocol is available upon request from the corresponding author. The consent process is entirely web-based and initiated through predetermined screening questionnaires on the landing website and the REDCap link. Participants are informed of the purpose of the study, procedures, benefits, risks, and their right to withdraw from the study without any penalty. Once a participant is determined to be eligible through the web-based process, they receive an electronic consent form for completion. Access to records of the consent forms is limited to only approved study personnel. Participants’ data will be deidentified before data analysis. Participants are assigned unique IDs instead of their names or identifiable information. Data are stored on the University of Alabama at Birmingham’s secured password-protected servers, with access restricted to study personnel only. Participants are compensated with two US $50 e-gift cards, one for baseline and one for 6-month follow-up. In addition, participants who participate in qualitative interviews are compensated with an additional US $50. The compensation is to acknowledge participants’ time and efforts without creating undue influence.

### Outcomes

#### Overview

All primary and other prespecified outcome measures are collected and stored through electronic surveys delivered by REDCap. The validated questionnaire packet is electronically delivered to participants at baseline and 6 months. Baseline and postintervention assessments will evaluate both primary and secondary outcome measures. Table 1 outlines all outcome measures and their validated instruments for data collection. HbA_1c_ results are transmitted from the testing company to study personnel and inputted directly into REDCap. Similarly, if participants self-report their HbA_1c_ results, study personnel will input them directly into REDCap. To maximize participant retention, reminder emails are regularly sent. Additionally, detailed notes are recorded for participants who discontinue the study.

#### Primary Outcome Measures

##### Quality of Life

Participants will fill out the Diabetes Quality of Life Measure, a 15-item questionnaire that explores perceptions regarding one’s capacity to manage diabetes alongside other aspects of life [39].

##### Psychological Distress

The Diabetes Distress Scale, a 17-item questionnaire evaluating emotional distress associated with diabetes, will be used to measure participants’ psychological distress. This scale has demonstrated validity and reliability in measuring diabetes-related emotional distress [40,41].

##### Self-Efficacy

Participants’ psychosocial self-efficacy in diabetes management is assessed using the Diabetes Empowerment Scale Short Form. This 8-item questionnaire explores attitudes concerning diabetes and the capability to effectively manage the condition. The Diabetes Empowerment Scale Short Form has exhibited validity and reliability as a measure of psychosocial self-efficacy [42].

#### Secondary Outcome Measure: HbA1c Levels

HbA_1c_ is measured using an HbA_1c_ test. HbA_1c_ results are transmitted from the testing company to study personnel and inputted directly into REDCap. Similarly, if participants self-report their HbA_1c_ results, study personnel will input them directly into REDCap. HbA_1c_ is measured both at baseline and at 6 months. The HbA_1c_ is a widely recognized test to assess the effectiveness of diabetes management strategies.

#### Other Prespecified Outcome Measures

##### Physical Activity

Physical activity is assessed through the Godin Leisure-Time Exercise Questionnaire. This brief questionnaire comprises 3 questions concerning strenuous, moderate, and light exercises undertaken within the past 7 days [43].

##### Dietary Intake

Participants will complete the UK Diabetes and Diet Questionnaire to evaluate nutrition and dietary behaviors over the past month. This questionnaire features foods commonly found in the United Kingdom. Therefore, to ensure clarity for participants from the United States, any UK-specific food item will be substituted with its equivalent US counterparts [44].

##### Medication Adherence

Participants will complete the Medication Adherence Rating Scale to assess their medication adherence. This general 10-item binary questionnaire asks participants about regular medication intake [45].

##### Health Dashboard Usability

To evaluate the usability of the telehealth dashboard, participants will complete the System Usability Scale. This Likert scale consists of items assessing the dashboard’s effectiveness (ability to accomplish tasks), efficiency (level of dashboard use), and satisfaction (subjective reactions to the dashboard) [46,47].

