## Methods

### Study Design

This study, called YumABLE, started in June 2024, when recruitment began, and is anticipated to end by fall 2025. The study is a 3-arm randomized controlled trial for evaluating the delivery of a 6-month intervention, which involves telecoaching, diabetes educational content, and technology access, to 90 individuals with diabetes and physical disabilities. The 3 intervention groups are a high-technology group, a low-technology group, and an attention control group. Study participants are adults aged 18 to 65 years with a permanent disability and T2D. All study groups receive an initial 60-minute 1:1 assessment, 4-weekly remote DSME classes, a make-up class option, and a follow-up class 3 months after the last DSME class. Each of the weekly remote classes as well as the follow-up classes are 90 minutes in length. The 3-month follow-up remote class is 60 minutes in length. DSME classes are organized into cohorts, with each cohort consisting of up to 10 participants. DSME classes and education will be of the same quality and quantity for all participants regardless of study group.

The difference among study groups is that the high-technology intervention group receives weekly diabetes-related materials delivered through multiple modalities (email, text, and telehealth platform), regular text reminders (to read the material, track health data, motivation, etc), and bidirectional SMS text messaging to enable timely communications with the certified diabetes care and education specialist (CDCES). Participants also have access to the telehealth platform. The low-technology intervention group receives 1 weekly email containing diabetes-related materials and bidirectional email communication with the CDCES. It does not have access to the telehealth platform. The attention control group, the “no technology” group, is only provided with DSME classes and has no technology support. It is not provided with any additional related content or access to technology-based support resources. Outcome measures are assessed at baseline and 6 months (Figure 1), with data collected from all intervention groups. Four weeks is considered a month in this study, making the study duration 24 weeks. Study activities are primarily conducted on the web nationally in the United States.

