**Other prespecified outcome measures**			
	Physical activity	Godin Leisure-Time Exercise Questionnaire	Baseline, postintervention
	Dietary intake	The UK Diabetes and Diet Questionnaire	Baseline, postintervention
	Medication adherence	Medication Adherence Rating Scale	Baseline, postintervention
	Health dashboard usability	System Usability Scale	Baseline, postintervention

^a^HbA_1c_: glycated hemoglobin.

After participants receive the initial survey packet, a member of the research team calls the participants within a week. The purpose of this call is to welcome participants into the study and go over study components. During the call, the research personnel informed participants that they will receive a laboratory requisition in their mail within a week, allowing them to visit a third-party clinical testing company location to have their blood glucose tested at no cost. The research staff also lets participants know that they will be randomized into 1 of the 3 intervention groups. Participants were not informed about which intervention was the primary focus or “intervention of interest” versus the comparator groups.

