### Randomization

After completing baseline surveys, participants are randomly assigned to 1 of 3 groups: the high-technology, low-technology, or attention control groups. The randomization sequence was created and stored in REDCap, automatically assigning participants to their respective groups with a 1:1:1 allocation ratio. The random allocation sequence was generated by study personnel using REDCap. Trained study staff enrolled participants and assigned them to intervention groups through the REDCap randomization module, which concealed the allocation sequence until assignment.

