## Results

We hypothesize that participants in the high- or low-technology intervention groups will show improvements in self-management behaviors related to T2D and self-efficacy compared to the control group at the 6-month follow-up. Again, we hypothesize that the high-technology intervention arm will result in better outcomes regarding reductions in HbA_1c_ than the low-technology and control arms. Additionally, we also hypothesize that the YumABLE intervention is feasible and acceptable to adults with permanent physical disability and T2D and that fidelity to the program will be maintained.

The development of the telehealth platform, which includes the dashboard and educational content, along with the creation of the landing website, has been completed by the study’s technical support team. In addition, research personnel have developed the database using REDCap to serve as the storage for data and communication tools such as emails and text notifications. The study began in June 2024. Since June 2024, intervention materials have been finalized, the IRB submissions have been completed, and participant recruitment began. In total, 28 participants have been enrolled and received the MNT and DSME remote class. Recruitment has ended, and we anticipate completing data collection by August 2025. Make-up classes were delivered to participants in any of the 3 cohorts between November 2024 and December 2024. The final 3-month follow-up classes were held for each cohort 3 months after the first class and were completed in February 2025. Data will be analyzed in fall 2025. Manuscript preparation and dissemination of study results are planned for spring 2026.

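### Table 1 schedules the dashboard usability scale at baseline, before anyone can have used the dashboard, and the text does not limit it to the one arm that gets access

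*Protocol article*

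**What the plan says.** Table 1, under the other prespecified outcome measures, has the row "Health dashboard usability System Usability Scale Baseline, postintervention". The Health Dashboard Usability section says "To evaluate the usability of the telehealth dashboard, participants will complete the System Usability Scale" and names no arm. Study Design says of outcomes in general: "Outcome measures are assessed at baseline and 6 months (Figure 1), with data collected from all intervention groups". The Outcomes overview adds: "The validated questionnaire packet is electronically delivered to participants at baseline and 6 months".

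On timing, the Randomization section says "After completing baseline surveys, participants are randomly assigned to 1 of 3 groups". On access, the Results section shows that the dashboard is part of the platform ("The development of the telehealth platform, which includes the dashboard and educational content"). Table 2 states for both the low-technology and the attention control arm: "Have no access to the telehealth platform". Only the high-technology row grants access.

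**The concern.** A usability scale measures a user's experience of a product. The article itself describes the items as covering task completion, extent of use and subjective reaction to the dashboard. Someone who has never had the dashboard has nothing to base an answer on.

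The Statistical Analysis section sets out paired tests of change from baseline to 6 months in each arm, and mixed models for repeated continuous outcomes, with no exception for this scale. Applied as written, they would produce a change score whose starting point refers to nothing.

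There is a second route to trouble. Respondents without access may sensibly skip the scale. They would then count as incomplete in the planned reports of instrument completion and missingness. The Sample Size section also brings in multiple imputation without saying which outcomes it covers. If it covers this one, it would create ratings of a product those people never had.

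**Working it through.** The article gives no figure for this scale, so there is none to reproduce. The check sets the schedule against access, then counts.

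**Schedule against access**

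| Time point | High-technology | Low-technology | Attention control |
|---|---|---|---|
| Baseline (before randomization) | no access yet | no access yet | no access yet |
| Postintervention | access | no access | no access |

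Only one of the six cells can give a rating based on use. The baseline row follows directly from Table 1 and the Randomization section. The two no-access cells in the postintervention row matter only if the scale is sent to all arms, which is how the Health Dashboard Usability and Study Design sections read together.

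**Inputs**
- Planned size: 90, with 30 per arm (Sample Size).
- Anticipated loss to follow-up: about 20% (Statistical Analysis).
- Participants reported as enrolled: 28 (Recruitment and Results). The abstract gives 90 recruited, so both totals are carried.
- Assumptions: an equal split for the 28, and the same loss in every arm.

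**Counts if all arms receive the scale at both times, 90 participants**
- Scheduled assessments: 90 × 2 = 180.
- From people with access: 0 at baseline + 30 postintervention = 30, and 30/180 = 16.7%.
- From people without access: 180 − 30 = 150, and 150/180 = 83%.
- Postintervention only: 60/90, or two-thirds, without access.
- Usable scores after loss: 30 × 0.8 = 24.
- Baseline-to-6-month pairs that can be interpreted: 0.

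**Counts with 28 participants**
- High-technology arm: 28/3 = 9.3, about 9.
- After loss: 9.3 × 0.8 = 7.5, so about 7 complete responders.
- Postintervention without access, before loss: 28 × 2/3 = 18.7, about 19.

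With equal loss in every arm, the two-thirds share does not change.

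**The case against.** The strongest reply is that the article may simply be loosely worded. It says participants, not all participants, and the Study Design sentence is a general one. Which arm receives a form specific to the dashboard is the kind of detail an article leaves to the full protocol, which is available on request. This stands in part: that every arm gets the scale is the plain reading of two passages together, not a stated rule.

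The second reply is that the scale may never have been sent at baseline. The Recruitment section describes the enrollment packet as demographics and the primary measures only. The Outcomes overview, where it says what the two assessments evaluate, names the primary and secondary outcomes and not the third group. Every row of Table 1 carries the same time-point entry, which would fit a label copied down the column. This also stands in part: a reader might infer that baseline usability data exist, and the documents do not settle it. It does not rescue the table, which states a baseline time point that cannot give a valid score. If the scale was not sent, the row is wrong. If it was, the data cannot be used.

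Third, a reader might infer that the acceptability hypothesis depends on this scale, or that a between-arm comparison of it is planned. Neither is supported. The analysis section ties feasibility, acceptability and fidelity to qualitative data, and no passage links the scale to that hypothesis. The generic tests do not name the scale, and the abstract's mixed-model targets are self-management behaviors, self-efficacy and HbA1c.

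**Conclusion.** The point holds in a limited form. The baseline entry for this scale in Table 1 is wrong as stated, because it precedes randomization and any platform access. No baseline score or change from baseline on it can be interpreted in any arm. This part needs no assumption.

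The part about arms is conditional. If the scale is given as the text reads, about two-thirds of postintervention scores come from people without access. Usable scores then number about 30 of 90, or 24 after 20% loss; with 28 enrolled, about 9, or 7 after loss. These counts rest on equal arms and equal loss. They also count people with access, which is not the same as people who used the dashboard.

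The consequence is modest. This is an other prespecified outcome, and nothing in the primary outcomes, HbA1c, sample size or randomization depends on it. The correction is still worth making, because the published schedule is wrong and the generic change analysis would otherwise apply to it.

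**What to change.** 1. Change the Table 1 row for "Health dashboard usability" to postintervention, high-technology arm, and say the same in the Health Dashboard Usability section.
2. Report the score descriptively, as a mean with a 95% confidence interval and the number of respondents.
3. Exclude any baseline or other-arm scores from change, between-arm and imputation analyses, and do not count those people as missing on this scale.
4. Reconcile Table 1, the Outcomes overview and the Recruitment section on what the baseline packet contained, and state whether baseline usability scores were collected.

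Data collection was expected to finish by August 2025, so altering the 6-month survey itself is probably too late. The work is one table row, one clarifying sentence and one analysis restriction, and no interpretable data are lost.

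There is one small cost. The Data Management section keeps the primary statistician blinded to allocation, and a score that exists for one arm only identifies that arm. The scale should therefore be kept in a separate file until the main analysis is done.
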